#### Metabolome analyses

4.7.6

##### Nuclear magnetic resonance (NMR) pipeline

4.7.6.1

To quantify metabolites in serum and stool of the participants, the untargeted metabolomics analysis will be performed with state-of-the-art NMR (nuclear magnetic resonance). Nuclear magnetic resnonance (NMR) spectroscopy was selected over other metabolomics pipelines such as mass-spectrometry (MS-) based approaches. Liquid chromatography (LC-MS) and gas chromatography (GC-MS) allow for comprehensive, untargeted metabolome profiling and analyses of specific metabolic pathways (127). However, the strength of NMS spectroscopy is that it provides a robust and highly reproducible platform for metabolomics, offering inherent quantitative accuracy regarding analytical stability, quantitative reliability, and data consistency (128, 129). NMR is therefore well suited for a longitudinal study design, allowing for excellent comparability of groups and timepoints. Metabolome analysis will focus on gut bacteria metabolites such as SCFA (e.g., butyrate), processed nutrients like polyphenols, folate, tryptophan and kynurenine metabolites, and metabolites of biochemical energy-pathways. Furthermore, choline and folate levels, lipids, and metabolites of inflammatory pathways and oxidative stress will be analysed.

##### NMR analysis of stool metabolites

4.7.6.2

For NMR analysis of stool metabolites, to account for inter-individual variability in fecal water content, an aliquot of each stool sample will be lyophilized, and metabolite concentrations and microbial abundances will be normalized to fecal dry weight. Samples will then be mixed with 500 with 500 μl NMR buffer in D2O and transferred into 5-mm NMR tubes. NMR measurements will be performed on an AVANCE™ Neo Bruker Ultrashield 600 MHz spectrometer equipped with a TXI probe head at 310 K. The 1D CPMG (Carr-Purcell_Meiboom_Gill) pulse sequence with water suppression using pre-saturation will be used for 1H 1D NMR experiments. Bruker Topspin version 4.0.2 will be used for NMR data acquisition. The spectra for all samples will be automatically processed (exponential line broadening of 0.3 Hz), phased and referenced using TSP at 0.0 ppm using the Bruker Topspin 4.0.2 software (Bruker GmbH, Rheinstetten, Germany). Spectra pre-processing and data analysis will be carried out using the state-of-the-art data analysis pipeline (group of [name] at Imperials College London) using Matlab^®^ scripts and MetaboAnalyst 4.0 (130). NMR data will be processed with Matlab^®^ vR2014a (Mathworks, Natick, Massachusetts, USA), and regions around the water, TSP, and remaining methanol signals will be excluded, and probabilistic quotient normalization will be applied to correct for sample metabolite dilution (131).

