#### Collection of biological samples

4.4.3

In order to collect the blood and stool samples, participants will be instructed to fast for at least 12 hours prior to venipuncture, and the blood samples will be drawn in the morning.

A maximum of 70 ml, equivalent to approximately 5 tablespoons of blood, will be collected into EDTA-coated tubes. Blood samples will be centrifuged at 4 °C for 15 minutes at 4000 rpm within 30 minutes of phlebotomy, and plasma aliquots will be immediately frozen at −80 °C until analysis.

Furthermore, approximately 1 g of stool will be collected from each participant in with stool sample kits with DNA/RNA stabilization buffer ensuring stabilization of microbial DNA at ambient temperature (OMNIgene^®^GUT, DNA Genotek Inc., Canada), immediately frozen and stored at -80 °C until further processing. For information regarding the further processing and downstream analyses of the biological data, see 4.7.5 and 4.7.6.

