#### Microbiome analyses

4.7.5

One gram of collected stool sample will be immediately stored in a -80 °C-freezer. Sequence analysis will be done according to the supplier’s recommendations. The workflow for microbiome analysis with Illumina MiSeq has already been described in detail in Klymiuk et al. (123). The Magna Pure LC DNA III Isolation Kit (Bacteria) (Roche, Mannheim, Germany) will be used to extract DNA according to manufacturer’s instructions. The hypervariable V3–V4 regions of the bacterial 16S rRNA gene will be amplified with Polymerase-chain-reaction (PCR) from total fecal DNA using the target-specific primers. 2µl of total DNA will be used in a 25µl PCR reaction in triplicates with the FastStart High Fidelity PCR system (Sigma, Germany). Cycling condition of initial denaturations at 95 °C for 3 minutes, followed by 30 cycles of 95 °C for 45 sec, 55 °C for 45 sec, 72 °C for one minute and a final elongation step at 72 °C for seven minutes. The resulting amplification products will be visualized on a 1.5% agarose gel and pooled, indexed and purified as described in Klymiuk et al. (123). The final library will be sequenced at ZMF Core Facility Molecular Biology in Graz, Austria, using an Illumina MiSeq desktop sequencer with v3 chemistry and 600 cycles (2x300). Unmapped bam files will be used as input for bioinformatics. To analyze the microbial community structure and taxonomic diversity, the obtained raw reads will be processed using Quantitative Insights Into Microbial Ecology (QIIME) scripts. During processing in silico, the FASTQ files will be paired, demultiplexed, dereplicated, and quality controlled. Further processing will include the use of the DADA2 algorithm (124) for sequence inference and chimera removal. Low-abundance features will be removed below a threshold of 20 total counts and presence in less than 5 samples. Sequences will be aligned against the SILVA 132 database, using the Scikit-learn classifier for taxonomic identification. The MAFFT software will be employed for *de novo* multiple alignment; the resulting alignment will be further treated with FastTree for phylogenetic tree construction (125). The Pielou’s Evenness Index considers species evenness and is similar to the Shannon-Wiener diversity model. Besides, Faith’s Phylogenetic Diversity (PD) accounts for phylogenetic differences among species. Numbers of detected species will be used for approximating richness, and Shannon Index for overall diversity estimates. Analyses of alpha diversity will be done in R (4.2) and RStudio. The pairwise Kruskal-Wallis test will be used to make statistical comparisons between the smoking cessation intervention and control groups.

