
For beta diversity, db-RDA will be performed on Bray-Curtis, Jaccard, and UniFrac distance matrices (weighted and unweighted) to compare the structural similarities between groups’ microbiomes. Beta diversity indices will be visualized with PCoA plots using Bray-Curtis and Jaccard dissimilarities. The Firmicutes/Bacteroidetes (F/B) ratio will be calculated from the rarefied feature table. Using this, MaAsLin2 will be used to detect differentially abundant taxa and further test associations with variables of interest such as cigarettes per day or metabolic markers (126). Identifications of microbial biomarkers will then be done applying LeFSe both in longitudinal and cross-sectional comparisons. This will be furthered to detect significant differences between groups in the microbial taxonomic abundance using the Analysis of Composition of Microbiomes’ ANCOM-BC implemented within QIIME2 (119).

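### Stool normalisation: dry-weight scaling cannot give 16S abundance per gram, and for metabolites the later quotient normalisation removes it

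*Protocol article*

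**What the plan says.** Section 4.7.6.2 of the protocol article (NMR analysis of stool metabolites) gives two normalisations for stool.

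- **Dry weight.** The stated purpose is "to account for inter-individual variability in fecal water content, an aliquot of each stool sample will be lyophilized", after which "metabolite concentrations and microbial abundances will be normalized to fecal dry weight". This comes before the NMR preparation, which begins "Samples will then be mixed with 500" (microlitres of buffer).
- **Probabilistic quotient normalisation (PQN).** At the end of the same section, during spectral processing, "probabilistic quotient normalization will be applied to correct for sample metabolite dilution".

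The microbiome data are described in section 4.7.5. The V3-V4 "regions of the bacterial 16S rRNA gene will be amplified with Polymerase-chain-reaction (PCR) from total fecal DNA", with 30 PCR cycles. Then "The resulting amplification products will be visualized on a 1.5% agarose gel and pooled, indexed and purified" before sequencing. No qPCR, spike-in or cell count is described, and the section has no dry-weight step. It also says: "The Firmicutes/Bacteroidetes (F/B) ratio will be calculated from the rarefied feature table". Differential abundance uses MaAsLin2, LEfSe and ANCOM-BC. Beta diversity uses db-RDA on Bray-Curtis, Jaccard and UniFrac distances.

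Section 4.7.6.1 names short-chain fatty acids (SCFA) as a focus of the metabolome analysis and justifies NMR by its quantitative accuracy.

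**The concern.** The sentence in 4.7.6.2 applies one rule to two kinds of data, and it does not deliver what it implies for either.

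Read totals from pooled amplicon libraries reflect sequencing depth, not the number of bacteria in the sample. Dividing them by a mass therefore does not give bacteria per gram. It attaches each sample's dry-weight factor to every taxon, and that factor then either drops out or remains as an artefact of stool water.

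For metabolites, both steps aim to remove one dilution factor per sample. When PQN follows dry-weight scaling, the first step leaves little or no trace. A reader told that concentrations were normalised to dry weight would take stool SCFA results as amounts per gram, although PQN output is on a relative scale. A change that raised all stool metabolites per gram in one arm would not be visible on that scale.

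**Working it through.** The plan gives no figure on this point to reproduce. The check is algebra, supported by a simulation of 100 samples with 200 metabolite signals and 80 taxa. The dry-matter fraction w is an **assumption**, drawn uniformly from 0.15 to 0.40; the article gives no value. The exact cancellations below do not depend on it.

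**1. 16S data.** Let c_ij be the reads of taxon j in sample i, and w_i the dry weight.

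- Proportions: (c_ij / w_i) / Σ_j (c_ij / w_i) = c_ij / Σ_j c_ij, so w_i drops out. Log-ratios and the F/B ratio lose it in the same way. Richness and presence/absence Jaccard depend only on which counts are non-zero.
- Simulation, with and without the division: relative abundance differs by at most 6e-17, Shannon by 9e-16, richness by 0, and centred log-ratios and an F/B-type ratio by less than 1e-14.
- Simulated read totals, drawn independently of bacterial load, correlated 0.07 with it. The division has no load information to work on.
- Unclosed Bray-Curtis: take two identical communities at equal rarefied depth, with w = 0.15 and 0.40. The distance is (1/0.15 − 1/0.40) / (1/0.15 + 1/0.40) = (6.667 − 2.500) / (6.667 + 2.500) = 4.167 / 9.167 = **0.45**. The correct value is 0.
- Rarefied table: rarefying cuts every sample to the same number of reads. After division by w_i the totals are unequal again and the entries are no longer counts. The F/B value is unaffected, but the table is no longer the one that section 4.7.5 describes.

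**2. Metabolites, in the written order.** PQN gives z_ij = x_ij / m_i, where m_i = median_j(x_ij / r_j) and r is a reference spectrum. Replace x_ij by x_ij / w_i. The numerator and m_i are both multiplied by 1/w_i, so z_ij does not change.

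| PQN variant | Effect of prior dry-weight scaling on the PQN output |
|---|---|
| Prior total-area scaling | none (maximum relative difference 7e-16) |
| Fixed reference | none (4e-16) |
| Cohort-median reference, no area scaling | after removing one constant common to all samples: residual log SD 0.012, range 0.96 to 1.03, against log SD 0.27 for dry weight |

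The small residual in the last row arises because the scaling changes the cohort reference itself. The article does not say which variant is used.

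**3. What is lost.** A uniform 30% rise per gram dry weight was simulated in one arm. The arm ratio was 1.30 after dry-weight scaling alone. With PQN on top it was 1.00 with total-area scaling and 1.01 without.

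**4. Reverse order.** Dividing by dry weight after PQN does not rescue the rule. PQN has already removed dilution, so the division puts the water factor back (correlation of mean log signal with log dry fraction −0.997).

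**The case against.** The best defence is that the sentence sits in the NMR section, while section 4.7.5 gives a self-contained microbiome pipeline with no dry-weight step. Most of the listed 16S methods are immune in any case. This largely stands. It means that the Bray-Curtis artefact is conditional on scaled values being used unclosed. It does not make the sentence correct, because the sentence names microbial abundances.

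On metabolites, lyophilising and weighing can standardise the material put into the tube, with PQN handling the remaining dilution. The text also assigns dry weight to concentrations and PQN to NMR data, so targeted SCFA values might never pass through PQN. The laboratory step is indeed not useless. But no passage says which normalisation yields the reported stool values, and the two rules as written give different scales.

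Three stronger readings are tempting, and the documents do not support them:

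- **All taxa shift between arms.** This would need an arm difference in stool dry matter, for which the article gives no figure, and unclosed values in the analysis, which it does not describe.
- **The dry-weight effect on PQN output is always exactly zero.** That depends on the unstated reference.
- **Stabilisation buffer contaminates the dry weight.** Section 4.4.3 says "approximately 1 g of stool will be collected from each participant in with stool sample kits with DNA/RNA stabilization buffer", but 4.7.6.2 does not say that the NMR aliquot comes from that kit, and the buffer's composition is not given.

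**Conclusion.** The point holds as a minor fault in a stated rule. For 16S data, dry-weight scaling cannot yield abundance per gram. It is inert for proportions, log-ratio methods, alpha diversity and Jaccard, would distort Bray-Curtis if left unclosed, and does not fit the rarefied table. The distortion of 0.45 rests on assumed dry fractions of 0.15 and 0.40 and shows the mechanism; it is not a forecast for this trial.

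For stool metabolites in the written order, PQN removes the dry-weight factor exactly with a fixed reference or prior total-area scaling, and almost exactly with a cohort-median reference. The quotient-normalised values are therefore not concentrations per gram dry weight, and a uniform per-gram change would be lost. A change confined to a minority of signals would survive, but in relative units.

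Plasma NMR (section 4.7.6.3) and the sample size (section 4.7.1) are unaffected.

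**What to change.** 1. In section 4.7.6.2, remove microbial abundances from the dry-weight sentence. Analyse 16S data as counts or relative abundances with the methods already listed in section 4.7.5.
2. Report targeted stool metabolites, such as SCFA, per gram dry weight **without** PQN.
3. Keep PQN for the untargeted PCA and O-PLS-DA profiles, state which reference it uses, and describe those results as relative.

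The cost is a change of wording and two output routes from the same spectra. It needs no new assay, sample or participants.

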##### NMR analysis of plasma metabolites

4.7.6.3

Blood plasma low molecular weight metabolites and lipoproteins will be also be analyzed on a Bruker 600 MHz Avance Neo NMR spectrometer. Plasma samples will be thawed, and 330 μl of each sample will be mixed with 330 μl of Bruker plasma buffer (Bruker, Rheinstetten, Germany). Following gentle mixing, 600 μl of the samples will be transferred into 5mm glass tubes and placed into a SampleJet rack (Bruker, Rheinstetten, Germany). Proton spectra will be ascertained at a temperature of 310 K using a standard nuclear Overhauser effect spectroscopy (NOESY) pulse sequence (Bruker: noesygppr1d), a Carr–Purcell Meiboom–Gill (CPMG) pulse sequence with pre-saturation during the relaxation delay (Bruker: cpmgpr1d) to achieve water suppression, and a fast scan 2D J-resolved (JRES) pulse sequence (Bruker: jresgpprqf). Data analyses will be carried out using Bruker IVDr Plasma (B.I.) module of the analysis software (Topspin version 4.1). Univariate statistical analysis of the concentration values for identifying lipoproteins and metabolites of interest differing between groups will again be carried out using MetaboAnalyst and the R package rstatix.

#### Methods of preventing bias

4.7.7

In the present study, several measures are taken to avoid bias. First, randomization is performed to ensure that participants are randomly assigned to the different groups. Furthermore, an experimental design with a control group that receives the usual treatment, allows a comparison with the intervention group. Additionally, all subjects are housed in the same facility where they receive the same treatments, meals, and – for the intervention group – the same smoking cessation intervention. These conditions ensure a high degree of uniformity and standardization, minimizing potential bias. Dietary factors, and confounders such as medication will be considered cautiously and explicitly (see 4.7.2 and 4.7.3).

## Work plan and timeline

6

**Table 3** displays the planned work timeline of the project.

**Table 3 T3:** Work plan of the project.

Work packages	Year 1				Year 2				Year 3			
	1-3	4-6	7-9	10-12	1-3	4-6	7-9	10-12	1-3	4-6	7-9	10-12
WP 1 Project management												
WP 2 Patient enrolment & clinical trial												
WP 3 Biomarker analysis												
WP 4 Statistical analysis & Bioinformatics												
WP 5 Publication & Dissemination												

green cells: engagement in respective activity

## Ethical aspects

7

The study will be conducted in accordance with the ethical guidelines of the Declaration of Helsinki as well as national and international regulations. It will be conducted according to the protocol and the requirements of the concerned regulatory authorities. Participants will be informed in detail about the objectives, methods, potential benefits and risks of the study. Participation is voluntary and based on a written declaration of consent. Participants’ personal data will be treated in strict confidence and used exclusively in anonymized form for data analysis. The risks related to the burden on participants include both psychological stress and physical discomfort that may be caused by nicotine withdrawal. However, given the participants’ willingness to quit smoking, they are consciously choosing a cessation program, which means the potential knowledge gain outweighs the temporary burdens of nicotine withdrawal. Furthermore, there will always be a clinical psychologist and a trained support system at ‘Grüner Kreis’ where the patients can receive professional guidance and support. As already mentioned in 4.6, providing a stool sample carries no risk. However, blood sampling can result in a bruise (hematoma), and depending on the condition of the veins, it can be more or less painful. This will be performed by an experienced study physician in accordance with WHO guidelines, who will also offer immediate support if necessary. The trial will be registered at the US-governmental repository www.clinicaltrials.gov before the enrolment of the first participant.

## Sex-specific and gender-related issues

8

In this study, sex, gender, age, and ethnic background do not influence the selection of the participants. It is aimed for a representative balance at all levels. However, it is possible that the number of male participants predominates, as they have been shown to have a higher prevalence of SUDs (132). Also, the preliminary data from the pilot study show a male predominance among study patients. Sex can evidently influence acute and long-term effects as well as side effects and treatment outcomes in SUDs, which is why sex as a variable will be incorporated in the statistical analysis plan (132, 133). Equal opportunities for all patients interested in participating in a smoking cessation intervention will be provided.
